### Missing data

Predictors with missingness exceeding 40% will be excluded from the RPM [40]. Missing data among the remaining predictors will be assumed missing at random, conditional on the available variables, and will be addressed using multiple imputation [41, 42]. Logistic regression models will be used to identify predictors of missingness that should be included in the imputation model. To identify the likely ability of the imputation model to accurately impute missing data, we will conduct exploratory analyses to examine associations between variables with missing data and available predictors.

The imputation model will contain all time to event, censoring, predictor, and auxiliary variables [43]. Predictor variables will be included in the imputation model in the same functional form as they will appear in the pre-specified prediction model (i.e., continuous, categorical). Auxiliary variables which can provide information on the missing values will be included to improve the accuracy of the imputations. For example, to facilitate the imputation of BMI, pre-pregnancy weight will be included in the imputation model as an auxiliary variable. The *mice* package in R will be used to generate 10 imputed datasets. The model will be generated in each imputed dataset and combined according to Rubin’s rules [41].

At model deployment when the outcome is unknown and when predictors may be unavailable, it will be necessary for the tool to impute missing predictor data in real-time using single or multiple imputation approaches, where feasible. To emulate multiple imputations in this setting, the model’s performance will be assessed in two sets of imputed datasets. The first set of imputed datasets will be derived using imputation models that include the outcome variables while the second set will be derived in imputation models that exclude the outcome variables. The assessment of model performance in the second dataset will more accurately describe likely performance at model deployment [44]. Should multiple imputations at deployment not be feasible, single imputation methods will be explored. The chosen single imputation approach for handling missing data at model deployment will be replicated during external validation to obtain an accurate assessment of likely model performance at deployment.

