### Main predictors

Table 1 lists the predictors and the pre-specified functional forms for each.

**Table 1 Tab1:** Pre-specification of predictors for risk prediction model

Variable type	Variable	Specification	df
Demographics	Age at index	Continuous variable	1
	Income quintile	Five categories	4
	Rurality	Binary: yes/no	1
	Immigrant status	Three categories (non-immigrant, previous (over 10 years ago), recent (10 years or less)	2
	Ethnicity	Three categories (South Asian, Chinese, Other)	2
Lifestyle	Pre-pregnancy BMI, kg/m^2^ (self-reported)	Continuous	1-3
Lifetime Health history	Previous mental health condition	Binary: yes/no	1
	Previous cardiovascular disease	Binary: yes/no	
Prior pregnancy history	Parity	Five categories (0, 1, 2, 3, > 3)	4
	Gravidity	Four categories (1, 2, 3, > 3)	3
	Previous GDM	Three categories: yes/no/NA	2
	Previous gestational hypertension or preeclampsia	Three categories: yes/no/NA	2
Index pregnancy	50 g oral glucose challenge test, mmol/L	Continuous	1-3
	GDM	Binary: yes/no	1
	Preeclampsia	Binary: yes/no	1
	Gestational hypertension	Binary: yes/no	1
	Caesarean-section	Three categories: planned/emergency/no	1
	Premature delivery	Binary: yes/no	1
Newborn	Birthweight	Continuous (for women with a multi-fetal birth, the child with the higher birthweight will be used)	1
	Large for gestational age (LGA) birthweight > 90th	Binary: yes/no (for women with a multi-fetal birth, any child with a record for LGA will be used)	1

Choice of the candidate predictors was informed by a systematic literature review, consultation with the project advisory board, clinicians, and the availability of the predictors within the study’s data sources. To enhance usability, predictors of the model were also chosen based on their likely availability to intended users of the model. Continuous variables with limited variation and binary variables with small counts will be excluded. While categorical variables have been pre-specified, frequency distributions will be examined and categories may be combined where there are small numbers. Interactions between all predictors and each of age, GDM and ethnicity will be considered for inclusion into the model due to expected differences in the effect of these predictors by the selected variables. Interactions which improve model fit will be included in the final model.

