### Model estimation

Model coefficients will be estimated using Weibull accelerated failure time models to calculate 5-year risk of type 2 DM. This parametric model was chosen since it allows for the calculation of more clinically meaningful parameters, including predicted survival time for different follow-up periods.

A full model, including all predictors and important interactions, will be developed in the first instance. Since the practical application of the full model may be time-consuming for intended users, we will derive a less complicated model by applying Ambler’s step-down approach [45]. This approach involves the regression of the derived prognostic index from the full model in the predictors. Predictors are subsequently dropped that produce the smallest reduction in *R*^2^. This procedure will be repeated until the exclusion of any further predictors would lead to a *R*^2^ value below 0.95. This approach will ensure that variables that contribute very limited information to the model are removed. We will verify our model building approach in exploratory analyses by applying least absolute shrinkage and selection operator (LASSO) to conduct variable selection and regularization.

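### The imputation model as described makes no provision for the interactions later selected by fit, so interactions with imputed predictors will probably be attenuated or distorted

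*Protocol article*

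**What the plan says.** Protocol article, Missing data. The contents of the imputation model are listed: "The imputation model will contain all time to event, censoring, predictor, and auxiliary variables". The form of the predictors is then fixed: "Predictor variables will be included in the imputation model in the same functional form as they will appear in the pre-specified prediction model". The bracket that follows explains what form means: "in the pre-specified prediction model (i.e., continuous, categorical". No product terms, stratified imputation or substantive-model-compatible method is named. The limit on missingness is: "Predictors with missingness exceeding 40% will be excluded from the RPM". BMI is expressly to be imputed: "to facilitate the imputation of BMI, pre-pregnancy weight will be included in the imputation model as an auxiliary variable". The Limitations section makes imputation of the oral glucose challenge test (OGCT) depend on exploratory checks.

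Main predictors: "Interactions between all predictors and each of age, GDM and ethnicity will be considered for inclusion into the model", because effects are expected to differ by these three variables. The selection rule is: "Interactions which improve model fit will be included in the final model".

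Model estimation: "A full model, including all predictors and important interactions, will be developed in the first instance". The Missing data section has the model built in each imputed dataset and then pooled, so the interactions are chosen on data that are already imputed.

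**The concern.** Suppose a predictor is imputed from a model in which its relation to the outcome is the same in women with and without GDM. The imputed values then carry one common relation into both groups. Mixed with the observed values, they dilute a true difference between the groups. If the predictor also varies more in one group than the other, a common imputation model misstates the within-group slopes and can produce a difference that does not exist.

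The selection step would then work on data in which real interactions are weakened and false ones may appear. The plan itself expects such interactions and names GDM status, ethnicity and age as its calibration subgroups. Calibration is to be assessed within the imputed datasets, so part of the check would rest on values drawn without the interactions.

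**Working it through.** **No figure in the plan to reproduce.** The plan gives no missingness rate, interaction size or OGCT spread. Its only design figure, a minimum of 6193 women, plays no part in this point.

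**How many interactions are at issue.** Table 1 sums to 32 main-effect df with BMI and OGCT linear, and 36 with 3 df each (previous cardiovascular disease, left blank, is counted as 1). Age and GDM have 1 df each and ethnicity has 2.
- At 32 df: 31 (age) + 31 (GDM) + 2 × 30 (ethnicity) = 122. Subtract the pairs counted twice (1 + 2 + 2 = 5), which leaves 117.
- At 36 df: 35 + 35 + 2 × 34 = 138, less 5, which leaves 133.

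**Simulation 1: the interaction coefficient.** Each run had 60,000 women, 40 replicates and 5 imputations, with a Weibull analysis model containing predictor × GDM. Values were missing completely at random. The imputation used main effects, the event indicator and the Nelson-Aalen hazard, by normal draws or predictive mean matching (PMM).

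Assumed inputs, not in the documents: GDM prevalence 8% (the Background gives 5 to 20%); interaction log hazard ratio −0.3, 0 or +0.3 per SD; residual SD ratio (GDM to non-GDM) 0.7, 1.0 or 1.5; 20% or 40% missing. The event fraction was 1.6 to 2.7%. For comparison, the Sample size section gives 2294 / 756,956 = 0.00303 per person-year, or about 1.5% over five years. The Monte Carlo standard error, reported for the normal-draw column, was 0.007 to 0.009.

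| True | SD ratio | Missing | Full data | No interaction, normal | No interaction, PMM | Within GDM strata |
|---|---|---|---|---|---|---|
| −0.3 | 1.0 | 20% | −0.277 | −0.231 | −0.240 | −0.281 |
| −0.3 | 1.0 | 40% | −0.277 | −0.179 | −0.198 | −0.272 |
| +0.3 | 1.0 | 20% | 0.315 | 0.226 | 0.250 | 0.297 |
| +0.3 | 1.0 | 40% | 0.315 | 0.145 | 0.196 | 0.290 |
| −0.3 | 1.5 | 40% | −0.283 | −0.215 | −0.281 | −0.279 |
| −0.3 | 0.7 | 40% | −0.270 | −0.156 | −0.084 | −0.264 |
| +0.3 | 1.5 | 40% | 0.309 | 0.081 | 0.064 | 0.240 |
| +0.3 | 0.7 | 40% | 0.324 | 0.106 | 0.308 | 0.316 |
| 0 | 1.5 | 40% | 0.013 | −0.049 | −0.104 | 0.006 |
| 0 | 0.7 | 40% | 0.030 | −0.017 | 0.112 | 0.032 |

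Attenuation = 1 − (imputed / full data). With equal spread:
- 20% missing: smallest 1 − 0.240/0.277 = 13%, largest 1 − 0.226/0.315 = 28%.
- 40% missing: smallest 1 − 0.198/0.277 = 29%, largest 1 − 0.145/0.315 = 54%.

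With unequal spread the direction is not fixed. PMM showed little or no attenuation in two cases (−0.281 against −0.283; 0.308 against 0.324), heavy attenuation in two others, and a false interaction of −0.104 or +0.112 where none existed.

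Imputing within GDM strata largely removed the problem, except for a positive interaction at SD ratio 1.5, where 1 − 0.240/0.309 = 22% remained. Adding only GDM product terms to a normal imputation with common spread was not enough: with no true interaction and 40% missing it gave +0.117 (ratio 1.5) and −0.113 (ratio 0.7).

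**Simulation 2: an auxiliary variable, and predicted risk.** This used a logistic outcome, 400,000 women, 4 replicates, GDM 8%, about 0.8% events and a true interaction of −0.35.
- With an always-observed auxiliary variable correlated 0.9 with the imputed one (assumed), attenuation was about 4% at 20% missing and 8% at 40%. Without it, attenuation was 17% and 37%.
- With 40% missing and no auxiliary variable, mean predicted risk was 2.15% against a true 2.11% in GDM women, and 0.69% against 0.69% in the others. The C-statistic was 0.706 either way.
- In the top OGCT decile of GDM women, predicted risk was 3.95% against 3.45%, an excess of 0.50 percentage points. At 20% missing it was 3.54% against 3.45%.

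**The case against.** The strongest reply is that this is a condensed article. Product terms and the imputation method are commonly left to an analysis plan, and the sentence on functional form shows an intention to match the prediction model. That would answer mere silence. Here, though, the article lists the contents of the imputation model and limits form to variable coding. The interactions are chosen by fit on the imputed data, so a form that is not yet known cannot be copied into the imputation. The mismatch follows from the plan as written.

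Other parts of the reply stand:
- A reader might infer that the plan prescribes main effects only. It does not say so; this is inferred from the listed contents and the bracket.
- A reader might infer that the interactions are always biased toward zero. The unequal-spread results show otherwise.
- The 40% figure is an exclusion limit, not an expected rate. OGCT may not be imputed at all.
- BMI is partly protected by pre-pregnancy weight, except where weight is also missing.
- A reader might infer that mean risk will be miscalibrated in the GDM, age and ethnicity groups. The documents do not show this, and Simulation 2 found GDM group means almost unaffected.

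Unequal spread is no defence of the plan. The Data sources section says the OGCT is used to screen for GDM, so equal distributions in the two groups cannot be presumed.

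**Conclusion.** The point holds in limited form. Followed as written, the plan imputes under a model that is not congenial with the model it feeds. Interactions with imputed predictors will probably be attenuated, by about 13-28% at 20% missing and 29-54% at 40% when spread is equal. They may be distorted in either direction when it is not. The consequence for predicted risk is expected mainly at extreme predictor values within subgroups, with little effect on group means or the C-statistic.

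These sizes rest on assumed missingness, interaction strength, spread and GDM prevalence, and on values missing completely at random. They illustrate the effect and are not estimates for this cohort. Only GDM interactions were simulated; extending the point to age and ethnicity rests on the same mechanism. It should be corrected before imputation, but it does not undermine the study.

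**What to change.** State in the Missing data section that imputation will accommodate the candidate interactions and spline terms of the incompletely observed predictors. There are two ways:

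- Preferably, use substantive-model-compatible full conditional specification with the candidate terms written in beforehand, and with the covariate model allowed to differ in spread by GDM status. The preference rests on the attenuation left by stratifying alone when spread is unequal; this method was not itself simulated.
- Otherwise, impute separately by GDM status and include age and ethnicity product terms within each stratum. GDM product terms alone should not replace the stratification.

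A substantive-model-compatible method conditions on the outcome, so it does not apply to the set imputed without the outcome. For that set, impute within GDM strata with age and ethnicity products.

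The cost is a few sentences, more imputation parameters and more computing time. With over 200,000 deliveries the extra parameters are a small burden.

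### The multiple-imputation check meant to emulate deployment removes only the outcome from the imputation model, so it may overstate performance wherever the tool lacks the auxiliaries or dropped predictors

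*Protocol article*

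**What the plan says.** All of the following is in the protocol article.

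- **Missing data**, content of the imputation model: "The imputation model will contain all time to event, censoring, predictor, and auxiliary variables". The example given is that "to facilitate the imputation of BMI, pre-pregnancy weight will be included in the imputation model as an auxiliary variable". Weight is not among the predictors in Table 1 (Main predictors).
- **Missing data**, emulation of multiple imputation at deployment: performance is assessed in two sets of imputed datasets. One is imputed with the outcome; for the other, "the second set will be derived in imputation models that exclude the outcome variables". No other removal is stated. The interpretation follows: "The assessment of model performance in the second dataset will more accurately describe likely performance at model deployment".
- **Missing data**, fallback if multiple imputation is not feasible: "The chosen single imputation approach for handling missing data at model deployment will be replicated during external validation".
- **Model estimation**: "Since the practical application of the full model may be time-consuming for intended users, we will derive a less complicated model". Predictors are dropped by Ambler's step-down until the next removal would take the approximation R² below 0.95.
- **Model presentation** places the calculator in electronic healthcare records as well as on the web. The **Discussion** says the web version is for women to use themselves.

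**The concern.** The outcome is left out of the second set because it is unknown when the tool is used. The same reason applies to any other variable the tool does not hold at that moment, but the rule names the outcome alone. On the natural reading, every candidate predictor, including those later removed by step-down, and every auxiliary still feed the imputation of a missing input.

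If the tool asks only for the reduced model's inputs, it must impute from less information than the evaluation used. The C-statistics and calibration reported as deployment performance would then be somewhat better than users obtain, chiefly for women with a missing input. A calibration slope that looks close to 1 could also hide a need for recalibration.

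**Working it through.** The protocol states no deployment C-statistic, missingness rate or auxiliary correlation, so there is no figure of its own to reproduce. The check has two parts.

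**1. Which variables each step uses**

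| Step | Outcome | Final-model inputs | Dropped predictors | Auxiliaries |
|---|---|---|---|---|
| Imputation for coefficient estimation | yes | yes | yes | yes |
| Second set, as written | no | yes | yes | yes |
| Reduced model in a web calculator | no | yes | not stated | not stated |
| Calculator in electronic records | no | yes | possibly in the record | possibly in the record |

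The second set matches deployment only if the two right-hand columns are available to the tool. No section says that they will be, or that they will not.

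**2. Direction and possible size (illustrative simulation)**

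Inputs from the documents:
- Sample size section: 2294 events in 756,956 person-years. Rate = 2294 / 756,956 = 0.00303 per year. Five-year risk = 1 − exp(−5 × 0.00303) = 1.5%.
- Missing data section: predictors with more than 40% missing are excluded, so 40% is the upper limit. I used 10% and 40%.

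Assumptions, not from the documents: 400,000 women; one BMI-like predictor missing completely at random; true coefficients known; log hazard ratios of 0.6, 0.6 and 0.5 per SD; correlation of 0.25 between BMI and the glucose challenge value; one auxiliary correlated r = 0.3, 0.6 or 0.9 with BMI and always observed; five stochastic imputations; calibration slope from a complementary log-log fit on one imputation.

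The outcome is excluded throughout. Each cell gives auxiliary kept / auxiliary removed, then the difference.

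| r | Missing | C, all women | C, women with the value missing | Calibration slope |
|---|---|---|---|---|
| 0.3 | 10% | 0.772 / 0.772 (0.000) | 0.694 / 0.694 (0.000) | 0.976 / 0.976 (0.000) |
| 0.3 | 40% | 0.752 / 0.749 (0.003) | 0.715 / 0.708 (0.007) | 0.892 / 0.884 (0.008) |
| 0.6 | 10% | 0.768 / 0.766 (0.002) | 0.727 / 0.704 (0.022) | 0.960 / 0.956 (0.004) |
| 0.6 | 40% | 0.755 / 0.746 (0.009) | 0.724 / 0.702 (0.022) | 0.911 / 0.873 (0.038) |
| 0.9 | 10% | 0.777 / 0.770 (0.007) | 0.770 / 0.708 (0.062) | 1.000 / 0.972 (0.028) |
| 0.9 | 40% | 0.773 / 0.748 (0.025) | 0.766 / 0.704 (0.063) | 0.992 / 0.889 (0.103) |

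Differences were taken before rounding. Low missingness shrinks the overall gap. With a moderate or strong auxiliary it does not shrink the gap among the women whose value is missing.

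A second illustration modelled weight directly: 600,000 women, assumed weight–BMI correlation 0.93, BMI hazard ratio 1.06 to 1.09 per kg/m², 10–40% missing, weight known whenever BMI is missing. It gave an overall C gap of 0.002–0.011 with risk averaged over draws, or 0.003–0.019 per draw, and 0.013–0.038 among women with BMI missing. The imputation R² for BMI was 0.87 with weight and the other predictors. Because 0.93² = 0.865, nearly all of that comes from weight. Neither exercise isolates the effect of predictors dropped by step-down.

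**The case against.** The strongest reply is that no section says the tool will lack these variables. An electronic record may hold weight and the dropped predictors even when the final formula does not use them. Table 1's predictors were also chosen partly for their likely availability to users, and a calculator that computes BMI from height and weight would hold weight. This stands. A reader might infer that the tool will not have these variables and that deployment performance is therefore too favourable, but the documents support only "may". The inference is plausible for a reduced model in a web calculator and weaker inside electronic records.

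Second, the Missing data section already commits to replicating the chosen single-imputation approach in external validation. This also stands and narrows the point to the multiple-imputation route and the Ontario assessment.

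Third, the protocol says only that the second set describes deployment more accurately, and relative to imputation with the outcome that remains true. But the declared purpose is to emulate multiple imputation at deployment, and the set does that only if the tool holds every imputation variable.

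A reader might also infer that the choice between multiple and single imputation would rest on an inflated C-statistic. The text does not support this: the choice is made on feasibility.

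Finally, the full variable list may belong in the full plan. However, the article does fix a rule (remove the outcome) and attaches an interpretation to it, so the rule itself is open to comment.

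**Conclusion.** The point holds conditionally. As written, the second set removes only the outcome. If the deployed tool lacks some of the remaining imputation variables, that set may overstate C-statistics and calibration for women with missing inputs. If the tool holds them all, there is no overstatement from this source.

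The size cannot be determined from the documents. Under the assumptions shown it runs from nil (weak auxiliary) to about 0.025 in overall C, about 0.06 in C among women with the value missing, and about 0.10 in calibration slope. The overall C and slope maxima need a strong auxiliary at the protocol's 40% limit. All of these shrink if weight tends to be missing together with BMI, because weight then cannot help the imputation. The effect of step-down-dropped predictors is argued from the text and not quantified.

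**What to change.** In the Missing data section, define the second set as imputed without the outcome **and** using only variables the deployed tool will actually hold: the final model's inputs, plus any auxiliaries or dropped predictors that the tool will collect or draw from the record. If the web calculator and the record-based version will hold different variables, say which one the set represents. Apply the same imputation specification in the Alberta validation on the multiple-imputation route too. Keep the rich imputation model, with outcome and auxiliaries, for estimating coefficients.

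Removing all auxiliaries and dropped predictors regardless would go too far, since it would understate performance where the record supplies them.

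The cost is a sentence or two of text and one extra imputation run. Reported deployment performance may be slightly less favourable.
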